### Data quality assurance measures

We will examine the cause of death of every patient in the practices over age 50 years who dies during the study, to ensure that all cardiovascular deaths are recorded appropriately in searchable form prior to outcome data extraction. Any patient recorded as having more than one cardiovascular event during the study will have their clinical record examined, to identify patients who have had the same event recorded twice (which may happen when a consultation for a stroke, TIA or myocardial infarction is mistakenly labelled as a "new episode" rather than a "review"). This process will be carried out both on controls and intervention patients. In addition, we will examine the notes of any patient who has a record of an event dated within 4 months of registration with a practice, in case this event occurred in the past but was incorrectly dated when the patient registered.

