### Intervention – the "e-Nudge"

The e-Nudge is an automated feedback system that examines information already contained in practice databases to help practice teams target preventive interventions towards the individuals most likely to benefit. At the same time, the e-Nudge identifies clinically important missing risk variable values and patients with possible undiagnosed diabetes. Designed to run as a series of updated alert messages and searches that use most recent risk variable values, it is able to track practice populations over time as patients enter and leave the area, grow older, and enter practice disease registers, such as those for diabetes, CHD, or stroke. It recognises that risk profiles are dynamic, and that "one-off" estimates of risk in individuals are liable to become outdated [33].

The alert messages will arise automatically through EMIS software when a high risk patient's notes are opened, and are continuously updated in real time. To identify patients who may not present to the practice, electronic searches will be undertaken every eight weeks. The purpose of both alerts and the lists is to trigger awareness of individual patients' risk within the practice team, and not to dictate specific treatments. The "e-Nudge" is therefore simply the feedback of this information. The resulting action is at the discretion of the practice team, and can be tailored both to the time available, and to the needs and preferences of the individual patient in the context of the clinician's broader knowledge of co-morbidity, current medication, and past response to treatment. The practice teams will have the following notifications for intervention patients identified in the searches.

**1 The eight-weekly search result is presented to a nominated member of the primary care team **under the six group headings.

**2 Alert messages **are displayed automatically on the computer screen each time the patients' electronic notes are opened. These are triggered for those identified in any of the groups:

• Group 1 patients: ***This CHD/Stroke/Diabetes (state which) patient's (BP) or (serum cholesterol) level (specify which) is out of the target range***.

• Group 2 patients: ***This patient may be at high cardiovascular risk, but values for the following risk variables were either missing or out of date: (specify which variables)*.**

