2. A new stroke or transient ischaemic attack (TIA) (whether or not already on the Stroke register)

3. A new myocardial infarction (whether or not already on the CHD register).

4. Sudden death from cardiovascular disease.

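### The duplicate-event check needs two events during the study, so a pre-study stroke, TIA or MI miscoded once as new is counted in the primary outcome unchecked

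*Protocol article*

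**What the plan says.** Under *Outcome analysis*, the protocol takes its outcomes from searches of the practice databases.

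Appendix 5d defines the events. First entry onto the CHD or stroke/TIA register counts. So do "A new stroke or transient ischaemic attack (TIA) (whether or not already on the Stroke register") and "A new myocardial infarction (whether or not already on the CHD register"). Under *Sample size calculation*, the paragraph on event rates confirms that a second stroke is a new event.

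*Data quality assurance measures* sets three checks:

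- **Deaths.** "We will examine the cause of death of every patient in the practices over age 50 years who dies during the study", so that cardiovascular deaths are recorded in searchable form.
- **Repeat events.** "Any patient recorded as having more than one cardiovascular event during the study will have their clinical record examined". The aim is to find one event recorded twice, an error the protocol attributes to a follow-up consultation being labelled a new episode instead of a review.
- **Recent joiners.** "we will examine the notes of any patient who has a record of an event dated within 4 months of registration with a practice". The reason given is that an old event may have been wrongly dated at registration.

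On the repeat-event check it adds: "This process will be carried out both on controls and intervention patients".

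**The concern.** The trigger does not match the error that it is meant to catch. A follow-up visit can be miscoded as a new episode whether the real event happened during the study or before it. The check looks only at patients with two or more events inside the study window. If the real event came before the study, one miscoded review leaves a single in-study event and the record stays closed.

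Register status does not screen the false event out. A patient already on the register cannot count again as a new register entry, but the stroke/TIA and MI items apply regardless of register status.

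What is at stake is the primary rate ratio. False events unrelated to treatment add to both numerators and move the ratio towards 1. The *Clinical significance* section requires the intervention rate to be at most 90% of the control rate. A true reduction of exactly 10% would therefore be expected to fall just short of that criterion.

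**Working it through.** **Step 1. Which records do the stated checks open?**

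| Patient's record | Opened? |
|---|---|
| True event in the study, then a review miscoded as new | Yes, two in-study events |
| Event before the study, two miscoded reviews in the study | Yes, two in-study events |
| Event before the study, one miscoded review and one true new event in the study | Yes, two in-study events |
| Event before the study, one miscoded review dated within 4 months of registration | Yes, registration check |
| Event before the study, one miscoded review dated later than that | **No** |

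The death check does not help in the last row, because it concerns how deaths are coded and not earlier non-fatal codes. This step needs no outside figures.

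**Step 2. The plan's event rate.** From *Event rates*: 451.77 + 569.77 + 187 + 51 = 1259.54, stated as 1260 per 100,000. The figure reproduces. It is an all-age rate, whereas the trial randomises people over 50.

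**Step 3. Over-50 rate.** Assumption, not in the documents: 35% of the list is over 50 and has 90% of the events.

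0.0126 × 0.90 / 0.35 = 0.0324, or 3.24 per 100 person-years in controls. With a true ratio of 0.90, the intervention rate is 0.90 × 3.24 = 2.916.

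**Step 4. False events.** Assumptions, not in the documents: 8–12% of over-50s have a prior stroke, TIA or MI, and 1–3% of these have one review miscoded per year.

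- Low: 0.08 × 0.01 = 0.0008, or 0.08 per 100 person-years; 0.08 / 3.24 = 2.5% of true control events.
- High: 0.12 × 0.03 = 0.0036, or 0.36 per 100 person-years; 0.36 / 3.24 = 11%.

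**Step 5. Observed ratio with equal error in both arms.** With false-event rate *f*, the observed ratio is (2.916 + *f*) / (3.24 + *f*).

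- Low: 2.996 / 3.32 = 0.902
- High: 3.276 / 3.60 = 0.910

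**Step 6. What a difference between arms would do.** This is purely hypothetical. With 25% more false events in the intervention arm:

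- Low: (2.916 + 0.10) / 3.32 = 0.908
- High: (2.916 + 0.45) / 3.60 = 0.935

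**A caution on denominators.** False events among over-50s must be set against an over-50 event rate. Setting the high value of 360 per 100,000 against the all-age 1260 would give (1134 + 360) / (1260 + 360) = 0.922, which overstates the dilution.

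**The case against.** The best reply is that the escape route is narrow and its effect small. Only a single isolated miscoding in a patient with a pre-study event gets through. Whether such patients are more exposed than those followed up after an in-study event is unknown. With equal error, the shift is at most about one percentage point even at the high end of the assumed range, and every input to that range comes from outside the documents. Equal dilution pulls the ratio towards 1, so it cannot create a false benefit. All of this stands. It limits the size of the point but does not remove the gap in the rule.

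A reader might also infer that the error is more frequent in the alerted arm, since alerts and lists direct attention to patients with established CVD. The documents do not support this:

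- The named error arises at consultations about a stroke, TIA or MI, whereas Group 1 alerts concern blood pressure or cholesterol and Group 6 alerts a missing glucose.
- "Alert messages are displayed automatically on the computer screen each time the patients' electronic notes are opened", so an alert does not itself create a contact. Only the eight-weekly lists are aimed at people who may not attend.
- Under *Control condition*, controls also receive Group 1 alerts where these are already usual care.
- Group 1 includes people with diabetes who may have no earlier event to recode.

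Some difference remains possible, because controls never receive the lists or the other alerts. Nothing in the documents establishes its existence or its size.

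**Conclusion.** The gap is real and follows from the text alone. The protocol names a coding error, sets a trigger for it, and that trigger misses patients whose event preceded the study and who have one miscoded review more than four months after registration. Each such record counts as a primary event.

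The size is modest and illustrative. Under the assumptions in Steps 3 and 4, a true ratio of 0.90 would appear as about 0.902–0.910 with equal error in both arms. A greater frequency in the alerted arm would bias the result further against the intervention, but the documents do not show that it occurs, so the 0.908–0.935 range is a what-if and not part of the finding. The change is worth making because it is cheap and corrects a stated rule on primary-outcome ascertainment.

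**What to change.** In *Data quality assurance measures*, keep the existing trigger and add a second: any patient with one or more stroke, TIA or MI codes during the study and any earlier code for the same condition, including before the study started. Find these patients with the same electronic search in both arms, and apply the existing record check without regard to allocation.

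The cost is one search condition and what should be a modest number of extra record checks. The documents do not allow that number to be estimated, but a count from the search would settle it before the work begins.

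A comparison limited to events in patients with no earlier code of the same type could be added without any record review. It should be a sensitivity analysis only. It also drops the genuine recurrences that Appendix 5d and the event-rate paragraph deliberately count, so it cannot isolate miscoding or replace the record check.

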### Overview of study design

This is a randomised controlled trial to test the effect of an automated electronic feedback system on CVD prevention in general practice. The practice populations over the age of 50 years will be randomised into two groups: "intervention" and "control". Intervention patients currently belonging to one of the high risk search groups described below will have alert messages appear on the screen when their electronic notes are opened. We will also apply an electronic search protocol every eight weeks to both groups throughout the study, to produce continually updated lists of potentially high risk patients for cardiovascular events. For the intervention group the patients on these lists will be revealed to the practice. The clinical software company EMIS, who serve the majority of practices in Warwickshire and Coventry, have programmed their software to produce the alerts and the eight-weekly lists for intervention patients. This "intervention" involves the feedback to practice teams to identify patients who are currently at high estimated risk, patients whose data is incomplete (who may benefit from updated measurements of cholesterol, blood glucose, blood pressure or recording of smoking status) and those who may have undiagnosed diabetes, through the alert messages and the eight-weekly lists. The control group will receive the usual care provided under the nGMS contract. No information will be withheld from the clinicians regarding control patients, the only difference will be the absence of reminders to draw their attention to the information. The practice teams themselves will decide on any changes in treatment in consultation with individual patients in both arms of the study, allowing care to remain tailored at the clinician-patient level. Outcomes will include the number of cardiovascular events and the number of high risk patients in the two populations (defined by inclusion on the eight-weekly search results). The design of the search protocol and the justification for the thresholds are described in the appendix.

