### Randomisation

Participating practice patients over 50 years of age will be randomised into two groups – "intervention" and "control." Patients will be consistently allocated to these groups throughout the study using an electronic technique that is concealed to all researchers and practitioners involved. This process will occur electronically during each search, so that those who join the practice during the study will be randomised automatically as soon as they are first provided with electronic notes as a fully registered patient. Temporary residents are not included in the study.

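### Event review is not stated to be masked, and e-Nudge alerts can show the reviewer the arm of some intervention patients

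*Protocol article*

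**What the plan says.** Protocol article, Data quality assurance measures, sets up three checks before the outcome data are used.

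- **Repeat events.** A patient with more than one recorded cardiovascular event "will have their clinical record examined, to identify patients who have had the same event recorded twice". The article then adds: "This process will be carried out both on controls and intervention patients".
- **Events soon after registration.** "we will examine the notes of any patient who has a record of an event dated within 4 months of registration with a practice". The aim is to catch old events that were given a wrong date.
- **Deaths.** "We will examine the cause of death of every patient in the practices over age 50 years who dies during the study", so that cardiovascular deaths can be found by the searches.

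The alert mechanism is described in two places. Overview of study design: "Intervention patients currently belonging to one of the high risk search groups described below will have alert messages appear on the screen". Intervention – the e-Nudge: the alerts "are displayed automatically on the computer screen each time the patients' electronic notes are opened".

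The Randomisation section says that patients are allocated "using an electronic technique that is concealed to all researchers and practitioners involved". The Control condition section lets controls keep Group 1 alerts in practices where these are already usual care. Outcome analysis limits searches and alerts to two years, with a third year of outcome collection. The data monitoring committee section has outcomes assessed annually.

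**The concern.** The repeat-event and early-event reviews decide whether a recorded event stays in the primary outcome. They are done by opening patient records, and in this trial an opened record can display the intervention itself. The article describes both procedures and says nothing that keeps them apart.

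If a reviewer can tell that a patient is in the intervention arm, a doubtful second stroke or a doubtful date may be handled differently from the same case in a control. Any such difference feeds directly into the comparison of event rates, where the target is a 10% reduction. A later masked analysis could not undo it, because the decision would already be built into the event file.

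**Working it through.** **1. Do the reviews change the outcome?** Yes. Appendix 5d counts a new stroke, TIA or myocardial infarction even in a patient already on the register. The repeat-event review must therefore separate a true recurrence from a miscoded follow-up consultation. The early-event review can remove an event as belonging to the past.

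**2. Whose arm can be seen while alerts are running?**

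| Record opened | Alert shown | Arm revealed? |
|---|---|---|
| Intervention, flagged in any of Groups 2–6 | Yes | Yes |
| Intervention, Group 1 only, practice does not use such alerts as usual care | Yes | Yes |
| Intervention, Group 1 only, practice uses them for controls too | Yes | No |
| Intervention, not currently flagged | None | No |
| Control, Group 1 criteria met, practice uses them as usual care | Group 1 | No |
| Any other control | None | No |

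Reviewed patients have a recorded cardiovascular event, and Groups 2–4 are defined for people without known cardiovascular disease or diabetes. The relevant alerts are therefore mainly those of Groups 1, 5 and 6. The article does not say how many such patients would be flagged.

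**3. When does review happen?** No date is given. Review after the alerts stop would show none. The annual outcome assessment makes review during the alert period possible but does not establish it.

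**4. Do the stated safeguards cover this?** The concealment statement concerns the allocation technique, and an on-screen alert bypasses it. Reviewing both arms gives equal coverage but does not mask the reviewer. That sentence also precedes the early-event check, so it does not clearly extend to it.

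**5. Scale, as illustration only.** The plan's rate reproduces: 451.77 + 569.77 + 187 + 51 = 1259.54, stated as 1260 per 100,000. Its sample size also reproduces: (1.96√0.0126 + 0.8416√0.01386)² / 0.00126² = 64,133.46, and × 1.1 = 70,546.80. This point changes neither figure.

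Assume 1:1 allocation of a list of 70,000, two years and no true effect:

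- Events per arm E = 35,000 × 2 × 0.0126 = 882. The target 10% difference is 88.2 events.
- The 70,000 is an all-ages list, while only patients over 50 are randomised. At the plan's rate, 882 therefore includes some events outside the trial population.

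Let f be the share of events reviewed and g the extra share of reviewed events wrongly removed in the intervention arm. Both are assumptions; the documents give neither.

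RR = 1 − f·g; SE = √(1/E + 1/(E·RR)); Z = ln(RR)/SE; two-sided type I error = Φ(−Z − 1.96) + Φ(Z − 1.96).

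| f | g | Events moved | RR | Type I error |
|---|---|---|---|---|
| 5% | 5% | 2.2 | 0.9975 | 0.050 |
| 10% | 10% | 8.8 | 0.99 | 0.055 |
| 10% | 25% | 22.1 | 0.975 | 0.083 |
| 20% | 25% | 44.1 | 0.95 | 0.186 |
| 20% | 50% | 88.2 | 0.90 | 0.577 |

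Because only some records reveal the arm, g is a product: the share of reviewed intervention events whose record reveals the arm, times the excess removal among those. For example, 40% revealing × 25% excess gives g = 10%. The lower rows therefore need both a high revealing share and a large excess. The bias could also run the other way, towards retaining intervention events.

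**The case against.** The strongest reply is that the article nowhere says review is unmasked. For an alert to influence a decision, four things must coincide: a live, alert-enabled screen, the alert period, a patient flagged at that moment, and an alert that identifies the arm. The article fixes none of them for the review. The triggers for review are set in advance and are the same in both arms. The questions are largely factual: whether a follow-up was miscoded, and whether a date is wrong. Login views and extract formats are also details that a journal article may leave to the full protocol.

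Much of this stands. It limits how many decisions could be affected and rules out any claim about the size of a bias. Fixed triggers also remove selective choice of cases. It does not remove the point, because the article goes beyond silence on masking. It specifies that records are opened to settle which events count, and that opening a flagged intervention record brings up the alert. Done as described while alerts run, the two procedures expose the arm for some patients.

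A reader might infer that outcome decisions in general are made with allocation visible. The documents do not support that: many intervention records show no alert, a missing alert does not identify a control, and a Group 1 alert is uninformative in some practices. A reader might also infer that cause of death is judged from alert-bearing notes. The article names only the cause of death as what is examined. It gives no source and does not say that notes are opened.

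**Conclusion.** The point holds in a limited form. The repeat-event and early-event reviews decide which events count, and no masking is stated. For intervention patients flagged at the time of a review done within the two-year alert period, the screen can reveal the arm. The exceptions are Group 1 alerts in practices that also use them for controls.

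The unmasking is partial and no bias is shown. The documents give no share of events reviewed, no share of reviewed patients flagged and no removal rates. The illustrated range, from almost no effect to one as large as the target, reflects the assumptions and is not evidence about this trial. This is a cheap improvement to the plan; it does not show that the primary comparison is invalid.

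**What to change.** In Data quality assurance measures, add that:

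- the repeat-event and early-event reviews are done on record extracts, or in a view of the record, with e-Nudge alerts and eight-weekly list membership suppressed;
- the same applies to the cause-of-death check if it uses live notes;
- each decision is recorded before allocation is linked to the event file;
- removed or reclassified events are reported by arm.

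The cost is the small work of preparing an alert-free view or extract, a sentence or two of text and a slightly slower review. The outcome definition, sample size and intervention stay as they are.

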### Sample size calculation

#### Event rates

Our study defines a cardiovascular event as a new diagnosis of CVD, a new myocardial infarction, a new stroke, a new transient ischaemic attack, or sudden death from CVD. A new stroke in someone with a previous stroke will count as a new event. An acute myocardial infarction in a patient previously diagnosed with angina will be recorded as a new event, but a new onset of angina in a patient who already had a diagnosis of acute myocardial infarction might not be recorded as a new diagnosis, as the patient will already be on the CHD register.

The British Heart Foundation [35] has compiled an estimate of the number of cardiac events in the UK population in 2002 from several available data sources. The number of myocardial infarctions (all ages) was estimated to be 268,000, while the number of new cases of angina (all ages) was estimated to be 338,000

The UK population was 59,321,700 in 2002 [Sources: Office for National Statistics, General Register Office for Scotland, Northern Ireland Statistics and Research Agency], so estimated incidence rates *for coronary heart disease *are

**Incidence of myocardial infarction **451.77 per 100,000

**Incidence of new case of angina **569.77 per 100,000

For *cerebrovascular disease*, the OXVASC study [36] provides a local source of information drawn from an Oxfordshire population. The incidence rates were:

**Incidence of stroke **187 per 100,000

**Incidence of TIA **51 per 100,000

Therefore

